## Statistical analysis

3

Statistical analysis will be performed using SPSS Statistics 26.0. Categorical data will be expressed as counts and percentages (n, %). Continuous data will be presented as mean ± standard deviation (x¯ ± s). The Mann-Whitney U test will be used to compare changes in each indicator between the two groups at 3 months and 6 months post-intervention relative to baseline. The Wilcoxon test will be employed to compare differences between the two groups at baseline and across four follow-up time points. Baseline demographic characteristics between the two groups will be compared using the chi-square test. A two-tailed test will be applied, and a P-value < 0.05 will be considered statistically significant.

If a reasonable amount of missing data is present, the data summary will indicate that the data are missing at random. In such cases, all analyses will incorporate multiple imputation procedures using baseline variables as auxiliary variables to address missing data. Linear regression and logistic regression will be selected for the imputation process, and the final analysis results will be combined to complete the imputation and analysis procedures.

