### Sample size

2.3

The sample size was calculated based on the primary metabolic indicator, serum Phe concentration. This study is a randomized controlled trial, with the intervention group receiving mobile health interventions and the control group receiving regular health education. The sample size ratio between the two groups is 1:1. According to a randomized controlled trial on PKU children based on a mobile health app (35), the blood Phe concentration in the control group was 360 μmol/L, while that in the intervention group was 260 μmol/L, with a standard deviation of 100 μmol/L in both groups. Using a two-tailed test with α = 0.05 and β = 0.1, the power (1-β) was set at 90%. Calculations performed using PASS 15 indicated that a minimum of 23 participants per group was required. Accounting for a 10% attrition rate, each group was expanded to 25 participants, resulting in a total minimum sample size of 50 participants.

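### The 90% power is worked out for Phe levels, but the stated test compares changes from baseline, so it holds only if baseline and follow-up Phe correlate at about 0.5 or more

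*Protocol article*

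**What the plan says.** Section 2.3 (Sample size) names the quantity behind the calculation: "The sample size was calculated based on the primary metabolic indicator, serum Phe concentration". The planning values come from a cited trial of a mobile health app in children with PKU: "the blood Phe concentration in the control group was 360 μmol/L, while that in the intervention group was 260 μmol/L". One common SD, 100 μmol/L, is assumed for the two arms. The error rates follow: "Using a two-tailed test with α = 0.05 and β = 0.1, the power (1-β) was set at 90" per cent. The result is that "a minimum of 23 participants per group was required", raised to 25 per group for 10% attrition. All of these inputs describe a concentration. None describes a change from baseline.

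Section 3 (Statistical analysis) states how the groups will be compared: "The Mann-Whitney U test will be used to compare changes in each indicator between the two groups at 3 months and 6 months", relative to baseline. It mentions no baseline covariate in this comparison. Baseline variables appear there only as auxiliaries for multiple imputation. A further sentence assigns a Wilcoxon test to differences between the groups at baseline and over four follow-up time points. The schedule in Tables 1 and 2 has only baseline, 3 months and 6 months.

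**The concern.** The power statement and the planned test refer to different quantities. The variability of a change score depends on how closely a child's follow-up Phe tracks the baseline value. If it tracks weakly, the change is noisier than the level and the test has less power than stated. If it tracks closely, the change is less noisy and the test has more. The article gives neither the correlation nor the SD of change, so a reader cannot tell which case applies.

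With 25 children per arm, the low end matters. A comparison with 60% to 75% power could well miss the 100 μmol/L difference that the trial was sized to detect. Baseline Phe is measured in every child, yet the stated between-group comparison does not use it as a covariate to gain precision.

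**Working it through.** **Inputs.** From section 2.3: difference 100 μmol/L (360 − 260), SD 100, two-sided α 0.05, 90% power, 1:1 allocation, 25 enrolled per arm, 10% attrition. From section 3: Mann-Whitney test on change, unadjusted. Assumed, because the article does not give them: normal data, the same SD of 100 at baseline and follow-up, and rho varied over a range. Attrition leaves 25 × 0.9 = 22.5 per arm, so 22 and 23 are both shown.

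**Step 1: reproduce the plan's figure.** For a two-sample t-test on levels, the noncentrality is 100 / (100 × √(2/n)) = √(n/2), on 2n − 2 degrees of freedom.
- n = 22: √11 = 3.317, power 0.8997
- n = 23: √11.5 = 3.391, power 0.9125

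So 23 is the smallest n that reaches 90% with a t-test on levels. That the t-test was used is inferred from this match.

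**Step 2: cost of the rank test alone.** A Mann-Whitney test on the same levels has power of about 0.88 at 22 per arm and 0.89 to 0.90 at 23. With efficiency 3/π relative to the t-test, 24 per group would be needed instead of 23. The loss is one to two points.

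**Step 3: effect of the change score.** With equal SDs, SD(change) = 100 × √(2(1 − rho)). This exceeds 100 when rho is below 0.5, equals 100 at 0.5 and is smaller above it. The Mann-Whitney powers are from 20,000 simulated trials. The required n uses the noncentral t with efficiency 3/π. The last column is an ANCOVA of follow-up Phe on group and baseline Phe, from 4,000 to 6,000 simulated trials, so its last digit may move by about one point.

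| rho | SD of change | Mann-Whitney on change, 22/arm | same, 23/arm | n per arm for 90% | ANCOVA, 22/arm |
|---|---|---|---|---|---|
| 0 | 141.4 | 61% | 62% | 46 | 89% |
| 0.3 | 118.3 | 75% | 78% | 32 | 92% |
| 0.4 | 109.5 | 83% | 83% | 28 | 93% |
| 0.5 | 100.0 | 88% | 90% | 24 | 95% |
| 0.6 | 89.4 | 94% | 95% | 19 | 98% |
| 0.7 | 77.5 | 98% | 99% | 15 | 99% |

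The planned test reaches 90% at rho of about 0.5 with 23 analysed per arm, and about 0.53 with 22.

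**Step 4: unequal SDs.** In general Var(change) = SDb² + SDf² − 2 × rho × SDb × SDf, where b is baseline and f is follow-up. Setting this equal to SDf² gives a break-even rho of SDb / (2 × SDf). If baseline SD were 150 against 100 at follow-up (an assumption), that is 150/200 = 0.75. At 22 per arm the planned test would then have 53%, 67% and 84% power at rho 0.3, 0.5 and 0.7, while the ANCOVA would have 92%, 96% and 99%. If baseline Phe were less variable than follow-up Phe, the break-even would fall below 0.5.

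**Step 5: why adjustment removes the dependence.** The residual SD in the ANCOVA is 100 × √(1 − rho²), which never exceeds 100. Based on this SD, the n per group for 90% power is 23 at rho 0, 21 at 0.3, 17 at 0.5 and 12 at 0.7.

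**The case against.** The best defence is that the direction of the mismatch is unknown. A correlation of 0.5 is moderate, and above it the planned test exceeds the stated power. With all 25 per arm analysed it has 92% at rho 0.5, and section 2.3 calls 50 a minimum total. The Mann-Whitney test on change keeps its type I error, randomisation balances regression to the mean in expectation, and a rank test tolerates skew. The ANCOVA figures assume normal data and a linear relation with baseline, and at rho 0.7 the two methods differ by about one point. All of this stands. It limits the size of the problem, but it does not supply the missing correlation or SD of change.

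A second defence is that the Wilcoxon sentence in section 3 could be read as a between-group comparison of levels at each visit, which is the quantity sized. That reading is possible. However, the sentence refers to four follow-up time points that the schedule does not contain, and it may mean a within-group test, so it does not clearly provide a levels analysis.

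A reader might infer more than the article supports:
- That the trial is underpowered, or that a strong correlation is needed. With equal SDs about 0.5 is enough. A higher value is needed only if baseline Phe is more variable than follow-up Phe, and the article does not report that.
- That the rank test is at fault. It accounts for one to two points.
- That the Phe classes in the Introduction, from 120 to 1200 μmol/L and above, show a wide baseline spread. They are diagnostic categories, not on-study baseline values. Wide stable differences between children would also tend to raise rho, which favours change scores.
- That the absence of a planned effect estimate with confidence interval is an error. A condensed article commonly leaves this to the analysis plan.

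**Conclusion.** The mismatch is real: section 2.3 sizes on levels and section 3 tests change. Nothing in the article ties the 90% to the planned test. With normal data and equal SDs, the stated power holds only if rho is at least about 0.5. With 22 completers per arm, power runs from about 60% at rho 0 through 75% at 0.3 and 88% at 0.5 to 98% at 0.7. A shortfall is possible but not demonstrated. The planned test is neither invalid nor biased. The point should be fixed because the remedy costs nothing and, under the same assumptions, the adjusted analysis had at least the power of the planned one at every correlation checked.

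**What to change.** In section 3, make the primary between-group comparison of serum Phe a baseline-adjusted analysis of follow-up Phe: ANCOVA on randomised group and baseline Phe, on the log or rank scale if the data are skewed. Keep the Mann-Whitney test on change as a sensitivity analysis. In section 2.3, add one sentence naming the analysis to which the 90% refers. If the change-score test stays primary, give and justify the SD of change (or the correlation and both SDs) and recompute the sample size from it.

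The cost is a few lines of text. No extra children, visits or measurements are needed, since baseline Phe is already collected, and the planned software fits the model.

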**Methods:**

This single-center, single-blind randomized controlled trial will be conducted at the Inner Mongolia Maternity and Child Health Care Hospital in China from March to September 2025. Participants will include children with PKU and their parents’ caregivers, who will be randomly assigned to either the intervention group (receiving mHealth interventions via WeChat) or the control group (receiving routine health education). The intervention will include health education, dietary management, regular monitoring reminders, and online consultation services. The primary outcome will be the serum phenylalanine and tyrosine levels of the children. Secondary outcomes will include nutritional indicators, intellectual development indicators, and the caregivers’ health knowledge, compliance, and mental health. Data collection will occur at baseline and at 3 and 6 months post-intervention.

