### Trial design and setting

2.1

The research will be conducted at the Inner Mongolia Maternity and Child Health Care Hospital in China from March 2025 to September 2025, employing clinical reagent testing and internationally recognized scales for quantitative investigation.

The study population consists of families of children with PKU, who will be divided into two groups: Group A will be the mHealth intervention group, while group B was the control group. The intervention group will receive mobile health interventions through WeChat group chats. The control group, on the other hand, will simply get regular health education, which includes an oral presentation on PKU by a professional physician at the time of enrollment, educating the parents of PKU children on how to manage their diets low in phenylalanine. A printed handbook on PKU disease and daily management knowledge will also be given to them, but they won’t have access to online education and training, frequent reminders for monitoring, or online consultation services.

The intervention will last for 6 months, with clinical indicators, intelligence tests, and questionnaire surveys being conducted at baseline, as well as at 3 and 6 months after the start of the intervention to examine the effectiveness of the intervention on the health management of children with PKU. The flow chart of the study is shown in **Figure 3** and **Table 1**.

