### Outcomes

2.8

Primary Outcomes:serum phenylalanine and tyrosine levels in children with PKU.

Secondary Outcomes:

Nutritional indicators: Height/length (cm), weight (kg), head circumference (cm), the concentration of hemoglobin, prealbumin, albumin, complete blood count (red blood cells, white blood cells, platelets), serum iron, ferritin, and 25-Hydroxy vitamin D3.Intellectual development indicators: For children aged ≤6 years, professional physicians will use the 0–6 Years Child Developmental Behavior Assessment Scale for evaluation. For children aged >6 years, IQ will be assessed using the Chinese version of the Wechsler Intelligence Scale for Children, Fourth Edition (WISC-IV).

In addition, considering that the health management of children with PKU may impose psychological and quality-of-life burdens on their parents’ caregivers (37, 38), the study also focuses on the following indicators for parents’ caregivers: PKU disease knowledge, compliance, mental health, family health, and family atmosphere, etc. Specific details are as follows:

Changes in PKU knowledge.Changes in parental compliance with health management: Measured by the number of dietary Phe concentration logs and the number of blood tests during the intervention period (39).Impact of health management on parental mental health: Includes levels of anxiety and depression, self-efficacy, and parenting stress.Changes in the family environment of PKU children: Includes specific behavioral changes such as family communication and broader indicators such as family health.

Socio-demographic variables will be collected from patients at baseline. Clinical reagent testing and questionnaires will be conducted at baseline as well as at 3 and 6 months of follow-up, with data collection times shown in **Table 2**.

**Table 2 T2:** Data collection components and collection timeline.

Type of research	Data collection		Timepoint		
			0M	3M	6M
Quantitative research	Sociodemographic variables	Gender, age, parental education level, parental occupation, monthly household income per capita, only-child status, presence of other PKU patients in the family	✓		
	Anthropometric variables	Serum phenylalanine(Phe)and tyrosine(Tyr)levels, height/length (cm), weight (kg), head circumference (cm), the concentration of hemoglobin, prealbumin, albumin, complete blood count, serum iron, ferritin, and 25-Hydroxy vitamin D3	✓	✓	✓

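### The Wilcoxon rule names four follow-up time points where the schedule has two, and the test either does not fit two independent arms or repeats the Mann-Whitney method on levels

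*Protocol article*

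**What the plan says.** The Statistical analysis section (section 3) holds two rules for testing outcomes. The first is "The Mann-Whitney U test will be used to compare changes in each indicator between the two groups at 3 months and 6 months", and it takes those changes relative to baseline. The second follows directly: "The Wilcoxon test will be employed to compare differences between the two groups at baseline and across four follow-up time points". It does not say whether the signed-rank or the rank-sum form is meant, whether levels or changes are tested, or how its result ranks against the first rule.

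The schedule is stated consistently elsewhere:

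- **Abstract, Methods:** "Data collection will occur at baseline and at 3 and 6 months post-intervention".
- **Section 2.1:** assessments are "being conducted at baseline, as well as at 3 and 6 months after the start of the intervention".
- **Section 2.8:** "Clinical reagent testing and questionnaires will be conducted at baseline as well as at 3 and 6 months of follow-up".
- **Table 2:** columns 0M, 3M and 6M.
- **Table 1:** the same three columns plus one recruitment column, -T1.

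On the group structure, section 2.3 says "The sample size ratio between the two groups is 1:1". Section 2.4 describes individual allocation by envelope, with no matching.

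**The concern.** A rule that tests outcomes should name visits that exist and a test that suits the comparison. This sentence does neither cleanly.

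Because Mann-Whitney is named separately one sentence earlier, an analyst may take Wilcoxon to mean the signed-rank test, yet the sentence describes a comparison between arms. Someone then has to decide what was intended, possibly after seeing data. The available readings lead to different analyses: a second between-arm test on levels, or a within-arm test that says nothing directly about the treatment effect. Both primary outcomes (serum phenylalanine and tyrosine) fall under the sentence.

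**Working it through.** **1. Count of time points.** The inputs are the schedule statements listed above.

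| What is counted | Number |
|---|---|
| Follow-ups (3M, 6M) | 2 |
| Assessments with outcome data (0M, 3M, 6M) | 3 |
| All columns of Table 1 (-T1, 0M, 3M, 6M) | 4 |
| Stated in the Wilcoxon sentence | 4 follow-ups, plus baseline |

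The stated four does not reproduce. Only the third row reaches it, but -T1 contains just eligibility screening and consent, and neither -T1 nor 0M is a follow-up.

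Extra visits after the intervention ends do not explain it either. Section 2.1 says "The intervention will last for 6 months" and places the research between March and September 2025. Two visits during the intervention and two more at 3 and 6 months after its end would need 6 + 6 = 12 months, and March to September is at most seven calendar months.

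**2. Which Wilcoxon test.**

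- *Signed-rank.* It works on differences within pairs. The arms are different families with no matching, so there are no pairs between arms. Run on 22 values against 23, as could arise after dropout, it fails outright.
- *Rank-sum.* This is the Mann-Whitney test under another name. On one simulated data set using the planning figures of section 2.3 (means 360 and 260, SD 100, 23 per arm), the two gave the same p-value, 2.128e-05 (large-sample form, no continuity correction). The method repeats, but the analysis need not, since it would be applied to levels while the first rule is applied to changes.
- *Within-arm change across visits.* Signed-rank would then be suitable, but the sentence says otherwise, and the result would not compare arms.

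**3. Size under the rank-sum reading.** Post-baseline between-arm p-values for the primary outcomes:

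- Change only: 2 outcomes × 2 visits = 4.
- Change and level: 2 outcomes × 2 visits × 2 tests = 8.

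The baseline comparison adds 2 × 1 = 2 more, which do not estimate a treatment effect.

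**4. Size under the within-arm reading, if the two arms' results were then set side by side.** Assume no true difference between arms and the same probability p of a significant within-arm change in each. Exactly one arm is significant with probability 2p(1−p). The documents give no value for p, so a range is needed:

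| Assumed p | 2p(1−p) | Intervention arm alone significant, p(1−p) |
|---|---|---|
| 0.05 or 0.95 | 0.095 | 0.0475 |
| 0.1 or 0.9 | 0.18 | 0.09 |
| 0.2 or 0.8 | 0.32 | 0.16 |
| 0.3 or 0.7 | 0.42 | 0.21 |
| 0.5 | 0.50 | 0.25 |

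The range is about 0.10 to 0.50. Half of it has the intervention arm as the significant one, which is the pattern that would seem to favour the intervention.

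**The case against.** The strongest reply is that the trial already has a usable between-arm rule. The Mann-Whitney test of change at 3 and 6 months matches the schedule and suits independent arms, and deleting the Wilcoxon sentence leaves it intact. That stands, and it limits the severity. A reader might infer that the plan has no runnable between-arm analysis, and the text does not support that.

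It can also be said that the sentence, read literally, points to the rank-sum test. On that reading it runs on levels at baseline, 3 and 6 months, and only the number four cannot be executed. That stands too. An analysis plan not shown here could name the form of the test. It could not reconcile four follow-ups with a schedule of two except by overriding this sentence.

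Three stronger readings are tempting, and the documents do not bear them out:

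- *That the two analyses conflict.* Levels and changes may agree. The text shows only that they are unranked.
- *That the error rate doubles.* The number of p-values doubles, but tests of level and change on the same outcome are correlated, so the error rate does not follow from the count.
- *That within-arm p-values will be read as a treatment effect.* Nothing says so, and the sentence speaks of a comparison between groups. The discordance figures show what that use would cost if it were made.

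None of this removes the wrong count or settles which test is meant.

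**Conclusion.** The point holds as an internal contradiction plus an ill-defined test, and should be fixed. The sentence states four follow-ups against two in every account of the schedule. Its test either needs pairs that the arms do not provide, or repeats the Mann-Whitney method on levels as a second between-arm analysis with no stated rank.

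The count of time points rests on the document alone. The rise from 4 to 8 primary p-values depends on the rank-sum reading. The 0.10 to 0.50 range depends on the within-arm reading, on assumed values of p, and on an informal comparison that the protocol does not propose.

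A reader might go further and infer that the Mann-Whitney analysis of change is itself wrong. This point does not show that: the test is valid under randomisation, and whether a baseline-adjusted analysis would be better is a question of preference.

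**What to change.** Delete the Wilcoxon sentence, or rewrite it so that:

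- the follow-up time points are 3 and 6 months;
- one named between-arm analysis per outcome governs the conclusion, either the Mann-Whitney test of change already stated or, preferably, a model adjusted for the baseline value that is collected anyway;
- any signed-rank test is labelled a within-arm description from which no treatment effect is concluded.

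If the Mann-Whitney rule is kept, the cost is one sentence. If the baseline-adjusted model is chosen, the Mann-Whitney sentence must change as well. Neither route needs more data, visits or participants. The choice should be recorded before outcome data are seen by arm.

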### Data collection

3.1

In this study, all data were gathered by professionally trained physicians from the Inner Mongolia Maternity and Child Health Care Hospital. These physicians conducted assessments of metabolic, nutritional, and intellectual development levels in PKU patients in strict adherence to the protocol guidelines. They also provided on-site assistance to families to help them complete the questionnaires. Furthermore, each family of PKU patients was assigned a unique code and registered to ensure that data from all follow-up points were accurately recorded on the pre-designed subject registration forms. The forms included fields for date and signature at the end to facilitate review and retrospective verification. Lastly, during the data analysis phase, a second review was conducted to identify and exclude any illogical or incomplete data entries.

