#### Stage 3: determine intervention content and implementation options—mobile health intervention based on the WeChat

2.6.3

Based on the analysis and selections from the previous two stages, and after comprehensively considering affordability, practicability, effectiveness acceptability, safety, and equity, the final decision is to utilize WeChat group chats for remote mobile health intervention. The group chat will incorporate the following four functions to achieve the seven interventions outlined in Stage 2:

*Health education module and real-time reminder function*. Through the WeChat group, educational materials in various formats (e.g., illustrations, videos) will be distributed weekly to provide PKU knowledge and health education. Topics include basic disease knowledge, the importance of health management, low-Phe diets, and regular follow-up monitoring. Personalized reminder notifications will also be set up to encourage timely completion of dietary records and regular medical check-ups.
*Diet uploading and phenylalanine content query function*. Parents will input the types and quantities of food consumed by their child each day into the WeChat group chat. The system will automatically calculate the daily Phe intake, notify parents if the intake exceeds the recommended limit, and provide adjustment suggestions. Additionally, the WeChat group will include a built-in food Phe database containing Phe content for common foods across three meals, along with recommended low-Phe meal combinations.
*Regular feedback and incentive mechanism*. The group chat will record the dietary logs and compliance status uploaded by parents. At the end of each month, virtual rewards such as badges and titles will be issued based on the monthly records to motivate parents to continue maintaining healthy management behaviors.
*Family interaction and online consultation function*. Parents can interact with other PKU families in the group chat to share health management experiences. Additionally, the group chat will offer an online consultation feature, allowing parents to seek advice from professional physicians in the group at any time.

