	Intellectual development variables	For children aged ≤6 years, professional physicians will use the 0–6 Years Child Developmental Behavior Assessment Scale for evaluation. For children aged >6 years, IQ will be assessed using the Chinese version of the Wechsler Intelligence Scale for Children, Fourth Edition (WISC-IV)	✓	✓	✓
	PKU knowledge	Questionnaire: Changes will be measured by a self-designed PKU theory scale	✓	✓	✓
	Parents compliance with health management	Measured by the number of dietary Phe concentration logs and the number of blood tests during the intervention period	✓	✓	✓
	The level of anxiety and depression on parents	Questionnaire: A simplified version of the Anxiety Depression Scale (PHQ-4)	✓	✓	✓
	The level of self-efficacy on parents	Questionnaire: A simplified version of New General Self-Efficacy Scale (NGSES-SF)	✓	✓	✓
	The level of parenting stress on parents	Questionnaire: The Parenting Stress Index (PSI-SF-15) and the Guilt about Parenting Scale (GAPS)	✓	✓	✓
	Family communication	Questionnaire: A Short Form of the Family Communication Scale (FCS-SF)	✓	✓	✓
	Family health	Questionnaire: A Short Form of the Family Health Scale (FHS-SF)	✓	✓	✓

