### Questionnaires

2.9

Socio-demographic and clinical data will be collected using self-designed questionnaires and the medical record system. Socio-demographic variables included gender, age, parental education level, parental occupation, monthly household income per capita, only-child status, and presence of other PKU patients in the family. Clinical variables included age at diagnosis, historical serum Phe concentrations, and intellectual development level.

Changes in PKU knowledge will be assessed using a self-designed PKU theory scale. This scale is adapted from the study conducted by Öztürk F et al. on the PKU knowledge of parents (40). It comprises 10 questions related to PKU, all of which are based on the information provided in Nelson’s textbook Classical Pediatrics to assess both correct and incorrect knowledge. Each question is scored as 1 point, with the total score ranging from 0 to 10. The development of the scale will be undertaken by the researcher, who will also complete its final validation. To determine the appearance validity and content validity, a pre-test will be administered to 20 randomly selected participants who did not take part in the final trial. These participants will be chosen from the recruited pool. The scale will be refined through pre-testing and expert review to ensure its robustness and reliability.

Depression and anxiety will be assessed using an ultra-brief screening scale for anxiety and depression (PHQ-4), which is a short, self-report scale used to assess an individual’s symptoms of depression and anxiety over the past 2 weeks (41). The scale comprises two dimensions: depression and anxiety, with a total of four items. The first two items assess depressed mood, while the last two evaluate anxiety. Each item is rated on a 4-point scale, with “not at all”, “a few days”, “more than half the days” and “almost every day,” corresponding to a score of 0, 1, 2, and 3, respectively, and the total score ranges from 0 to 12. Different levels of psychological problem were defined with scores: normal (0~2), mild (3~5), moderate (6~8), and severe (9~12). The Cronbach’s alpha of the PHQ-4 was 0.865, which is of high validity and reliability, in a study conducted in Chinese parents (42). Due to its brevity and efficiency, the PHQ-4 is a practical tool for healthcare professionals to quickly and effectively assess anxiety and depression in target populations.

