If this research plan proves effective, it can be extended to the health management of PKU patients in other regions of China. According to the data from the Chinese newborn screening information system from 2013 to 2017 (52), Gansu, Qinghai, Ningxia and Shanxi are among the provinces with the highest PKU incidence rates. Building on the development of PKU patient families in Inner Mongolia, a northern province, this study provides a set of referable intervention strategies for the health management of PKU patients in these provinces. Existing studies have established network-based programs for the health management of PKU patient families (35). These mobile health intervention platforms can be integrated with the theoretical model developed in this study to provide more personalized, convenient, efficient and cost-effective intervention plans for PKU patient families.

This study also has several limitations. First, due to the nature of the intervention, blinding of the interventionists is not feasible. To mitigate this limitation, detailed training and standardized intervention manuals will be provided to minimize subjective bias among intervention personnel, thereby ensuring consistency in the implementation of intervention measures. Second, some outcome measures rely on self-reported date from participants, which may introduce bias and affect the reliability of the results.

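### Hospital physicians help families complete the caregiver questionnaires, including a right-or-wrong PKU knowledge test, so the help itself can influence caregiver secondary outcomes

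*Protocol article*

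**What the plan says.** Section 3.1 (Data collection) states that "all data were gathered by professionally trained physicians from the Inner Mongolia Maternity and Child Health Care Hospital", and then: "They also provided on-site assistance to families to help them complete the questionnaires". It names no scale to which this does not apply and does not describe the kind of help. The same section says that incomplete entries are excluded at a second review.

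The questionnaires are listed in Table 2 (section 2.8) and described in section 2.9:

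- **PKU knowledge.** Table 2 has "Questionnaire: Changes will be measured by a self-designed PKU theory scale", at 0, 3 and 6 months. Section 2.9 says that the ten items are there "to assess both correct and incorrect knowledge", and "Each question is scored as 1 point, with the total score ranging from 0 to 10".
- **Mood.** The PHQ-4 is introduced as an instrument "which is a short, self-report scale used to assess" symptoms over the past two weeks.
- **Other caregiver scales.** NGSES-SF (self-efficacy), PSI-SF-15 and GAPS (parenting stress and guilt), FHS-SF (family health) and FCS-SF (family communication).

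On contact with physicians, section 2.6.2 has physicians train caregivers in the low-Phe diet, and section 2.6.3 gives WeChat families a consultation channel, "allowing parents to seek advice from professional physicians in the group at any time". Under section 2.1, controls receive one physician talk at enrolment and a handbook, and no online consultation. Section 2.4 has each family open its own allocation envelope. Section 4 says that interventionists cannot be blinded and lists as a further limitation that "some outcome measures rely on self-reported date from participants".

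**The concern.** A knowledge test measures the caregiver only if the caregiver answers it unaided. A PKU physician knows the answers to all ten items, so help with no stated limit can move the score directly. The mood, stress, guilt and self-efficacy scales have no right answer. There the worry is that a parent sitting with a physician from the child's own hospital gives the more acceptable answer. Completion with a physician's help is a different mode from the self-report described for the PHQ-4.

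Two features make equal influence in both arms uncertain. Families know their allocation. And the WeChat arm has ongoing access to physicians, while no section says that the physicians helping with forms are different people. This difference in contact arises after baseline, so the planned comparison of changes from baseline (section 3) would not remove an effect of it.

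At stake is the interpretation of the caregiver questionnaire outcomes, most of all knowledge, which is a direct target of the intervention.

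**Working it through.** **1. Which outcomes are exposed.** I set the outcome list in section 2.8 against the help described in section 3.1.

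| Outcome | How measured | Exposed to help with forms? |
|---|---|---|
| Serum Phe and Tyr (primary) | Blood test | No |
| Nutritional indicators | Body measurements, blood tests | No |
| Child development or IQ | Assessment of the child | No |
| Compliance | Counts of diet logs and blood tests | No |
| PKU knowledge | 10-item right/wrong questionnaire | Yes, most directly |
| PHQ-4, NGSES-SF, PSI-SF-15, GAPS, FHS-SF, FCS-SF | Rating scales | Yes, through the setting in which they are answered |

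**2. Figures in the plan.** The plan gives no SD or expected difference for any questionnaire. The only design figure that I use is 25 per group (section 2.3). Its base reproduces: with a difference of 100, SD 100, two-sided α 0.05 and 90% power, the two-sample t-test needs 22.02, rounded up to the stated 23 per group.

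**3. Unequal help, no true effect.** These inputs are assumptions: SD of the knowledge score 1.5, 2 or 2.5, and help that adds b points more in one arm than in the other. With n = 25 per arm (48 degrees of freedom), the noncentrality of the t-test is

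λ = b / (SD × √(2/n)), where √(2/25) = 0.283.

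For b = 1 and SD = 2, λ = 1 / (2 × 0.283) = 1.77. The chance of p < 0.05 is then 41%. The full range is:

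| Extra help in one arm | SD 1.5 | SD 2 | SD 2.5 |
|---|---|---|---|
| 0.5 point | 21% | 14% | 11% |
| 1.0 point | 64% | 41% | 28% |
| 1.5 points | 93% | 74% | 55% |

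The plan names the Mann-Whitney test. I simulated it on whole-number scores with an assumed mean of 6, limited to 0–10, and 10,000 trials per setting. At 1 point it rejects in about 60%, 38% and 26% of trials for SD 1.5, 2 and 2.5. With no extra help it stays near 5%. Across both tests the range at 1 point is about 26% to 64%. One point is one prompted item per family, on average.

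**4. Equal help, true effect present.** Suppose that a share h of wrong answers is corrected in both arms. A true mean m becomes m + h(10 − m), so a true difference d becomes d(1 − h). With assumed means of 6 and 8:

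| h | Control | WeChat | Difference |
|---|---|---|---|
| 0 | 6.0 | 8.0 | 2.0 |
| 0.25 | 7.0 | 8.5 | 1.5 |
| 0.5 | 8.0 | 9.0 | 1.0 |
| 0.75 | 9.0 | 9.5 | 0.5 |

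Equal help therefore works against finding a benefit.

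**The case against.** The strongest reply is that the sentence in section 3.1 may describe something harmless: handing out forms, reading items aloud, checking for blanks. The staff are described as trained, and the limits of their help could stand in a full protocol that is not shown. Much of this stands. A reader might infer that physicians supply or steer answers; the document does not say so, and no bias is shown. It does not follow that nothing needs changing. Physician-assisted completion is the stated mode of administration, and the proposal replaces that mode. The training and manuals mentioned in section 4 concern delivery of the intervention, not the questionnaires.

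The reply also says that the procedure is the same in both arms, so the test keeps its 5% level. That is correct if the help is equal. A reader might infer that the help favours the WeChat arm. No section says this, and none says that the WeChat physicians are the ones helping with forms. Nor are controls without physician contact: they have the talk at enrolment and are assessed by hospital physicians at each visit. What remains is that nothing rules out unequal help, and that equal help has its own cost in a compressed score.

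A reader might also extend the point to compliance. That is not supported, since compliance is a count of logs and blood tests.

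Finally, section 4 already concedes possible bias from self-report. It does so without mentioning any influence of the helper.

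**Conclusion.** The concern holds as a risk to caregiver questionnaire outcomes, chiefly the 0–10 knowledge score. It rests on three things in the text: physicians help with the forms without exception, families know their arm, and the helpers are not separated from those who train and advise the WeChat arm. The direction is open: unequal help could mimic a benefit, and equal help would mask one.

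The 26% to 64% at one point of unequal help only shows sensitivity. It depends on assumed SDs of 1.5 to 2.5, 25 per arm, no true effect and an assumed size of help. It applies to the knowledge scale and says nothing about the size of any effect on the other scales. All affected outcomes are secondary. This is a cheap improvement and does not threaten the trial's main conclusion.

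**What to change.** Change section 3.1 to provide that:

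- caregivers complete the questionnaires themselves, on paper or phone, before they see the physician;
- help is limited to reading an item aloud word for word, without explaining its content, and no help is given on the knowledge items;
- the form records each item that was read aloud;
- staff check the form for blanks and hand it back for completion without discussing answers.

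The last step matters because section 3.1 excludes incomplete entries, so in a trial of about 25 per arm blank items could cost whole questionnaires.

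If assessments have already been done with help, report what help was given, by whom and in which arm, and add it to the limitations.

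The cost is a few lines in section 3.1 and a short instruction on the form, with no extra staff. The downside is a few more blank items from caregivers with low literacy. It should be small, because section 2.2 requires caregivers to be able to use WeChat and to communicate normally, and several of the scales are short forms.
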